## Abstract

**Introduction:**

White spot lesions associated with orthodontic treatment are a common problem. Recent studies reported increased resistance to acid demineralization of enamel after sub-ablative CO_2_-laser irradiation in a combination with fluoride application. The aim of the study is to assess the efficacy of CO_2_-laser in combination with a fluoride varnish in the prevention, severity, and extent of white spot lesions during orthodontic treatment with fixed appliances.

**Methods and analysis:**

This is a protocol for a randomized, split-mouth controlled, clinical trial. The participants will be children aged 12–18 years at high caries risk, requiring fixed orthodontic treatment. The vestibular surfaces of maxillary anterior teeth of eligible patients will be exposed to CO_2_-laser irradiation in combination with fluoride therapy and fluoride therapy alone followed by bonding of orthodontic brackets. The patients will be recalled 6 and 12 months post-irradiation. Outcome measures will be visual examination with International Caries Detection and Assessment System criteria and SoproLife fluorescence. Data will be analyzed by Student’s *t* test for paired samples and proportional odds logistic regression model, *p*<0.05.

**Ethics and dissemination:**

The study protocol has been approved by the Committee for Scientific Research Ethics, Medical University-Plovdiv, Bulgaria (Reference number P-605/27.03.2020, Protocol of approval No. 2/01.04.2021) and registered on a publicly accessible database. This research received institutional funding from the Medical University–Plovdiv, Bulgaria. The results will be presented through peer-reviewed publications and conference presentations.

**Trial registration:**

ClinicalTrials.gov NCT04903275. Registered on June 2021.

**Supplementary Information:**

The online version contains supplementary material available at 10.1186/s13063-022-06117-y.

## Introduction

### Background and rationale

Orthodontic treatment leads to preferential growth of cariogenic bacteria due to the increase of biofilm accumulation, difficult oral hygiene, reduction of the self-cleaning mechanisms of the oral cavity [1, 2]. Orthodontic appliances, such as fixed braces, automatically place the patient at least at a high or extremely high risk of oral diseases [3]. In a recent study from 2020, Pinto et al. found that individuals undergoing fixed orthodontic therapy for 1 year had a significantly higher incidence and increase of active caries lesions than those without a fixed appliance [2]. The early development of the initial caries lesion in the enamel starts underneath a relatively intact superficial layer of the enamel surface. As a result of the process of demineralization, tissue defects appear in the enamel that correlates to the porous white opacities seen clinically. “White spot lesion” is the most commonly used term in dental literature to describe the subsurface enamel porosity as a result of carious demineralization [4].

The carbon dioxide laser (CO_2_-laser) is reported to increase the acid resistance of enamel due to changes in the hydroxyapatite crystals and the melting and recrystallization of the carbonated hydroxyapatite crystals [5, 6]. Several studies have suggested that CO_2_-laser is the most effective in the prevention of caries [6–10]. Furthermore, the results of recent studies reported increased resistance to acid demineralization of the enamel after sub-ablative CO_2_-laser irradiation in a combination of fluoride application [5, 11–16]. The synergistic mechanism of laser with fluoride is due to the removal of the organic matrix that would render a greater surface area for an increased fluoride uptake both superficially by forming calcium fluoride (CaF_2_) and in its crystalline structure [16, 17].

Most of the studies demonstrating the effect of CO_2_-laser and fluoride therapy on solubility or microhardness enhancement of enamel are in vitro [5, 12–14, 16, 18]. Few clinical studies investigating the efficacy of this newly developed laser irradiation pattern in the prevention of dental caries are retrieved [19, 20]. Therefore, the investigation of this synergetic effect of laser irradiation and topical fluoride application could be a good prophylaxis option and will improve the quality of dental care.

### Objectives

The aim of the study is to assess the viability and efficacy of the CO_2_-laser in combination with a fluoride varnish in the prevention, severity, and extent of white spot lesions during orthodontic treatment with fixed appliances in a randomized, open-label, split-mouth, controlled, clinical trial over 12 months. The mineral loss will be quantified by visual examinations with the International Caries Detection and Assessment System (ICDAS) and SoproLife® Daylight and Blue fluorescence.

### Trial design

The research is designed as a longitudinal randomized controlled clinical cross-over experimental study with a split-mouth design. This type of trial reduces the variability in trial outcomes, but patient recruitment is too difficult and often takes more time than expected. Table 1 presents the recruiting, allocation, interventions, monitoring, and analysis of the research in accordance with the Standard Protocol Items: Recommendations for Interventional Trials recommendations [21].

**Table 1 Tab1:** Trial design. The table summarizes the enrolment, allocation, interventions, and assessments in the trail

	Study period						
	Enrolment	Allocation	Post-allocation				
**Timepoint**^**a**^	**−** ***t***_**1**_	**0**	***t***_**1**_	***t***_**2**_	***t***_**3**_	***t***_**4**_	***t***_**5**_
**Enrolment**							
Eligibility screening	**×**						
Informed consent	**×**						
Allocation		**×**					
**Interventions**							
Topical fluoride application + CO_2_-laser irradiation				**×**			
Topical fluoride application (placebo manipulation)				**×**		**×**	**×**
Bonding brackets					**×**		
**Assessments**							
ICDAS score			**×**			**×**	**×**
*SoproLife*® Daylight fluorescence			**×**			**×**	**×**
*SoproLife*® Blue fluorescence			**×**			**×**	**×**

^a^Post-allocation time frame: *t*1, before the start of the treatment; *t*_2_, during laser irradiation/placebo manipulation; *t*_3_, orthodontic treatment; *t*_4_, 6 months after the laser irradiation, *t*_5_, 12 months after the laser irradiation

Due to the nature of the interventions, the doctor, dental assistant, and the patient are not blinded and the trial is an unmasked, open-label trial. The experimental manipulation includes topical fluoride application and CO_2_-laser irradiation of the left maxillary anterior teeth and topical fluoride application (placebo manipulation) to the contralateral teeth of the same patient.

## Methods and analyses

### Study setting

The study setting of this research includes the Department of Paediatric Dentistry and the Laser Centre of the Faculty of Dental Medicine, Medical University – Plovdiv, Bulgaria.

### Eligibility

#### Inclusion criteria

Participants in the study are 12–18-year-old children, in good general health;Children, requiring fixed orthodontic treatment (fixed braces);Children at high caries risk according to “Oral disease risk assessment tool” accepted and used in the Department of Paediatric Dentistry, Faculty of Dental medicine, Medical University – Plovdiv, Bulgaria (see supplementary data file S1 “Appendix for risk assessment of oral diseases”);Children with untreated non-carious vestibular surfaces of the six maxillary anterior teeth of the permanent dentition (central and lateral incisors, canines) with ICDAS code 0 [22–24];Verbal assent from the child willing to comply with all study procedures and protocol; andObtained written informed consent by the patient’s parent/guardian for participation in the study (see supplementary data file S2 “Patient consent form” and S3 “Information leaflet”).

#### Exclusion criteria

Children with systemic diseases that may affect oral health or oral microflora (such as diabetes);Children with medication intake that could affect the salivary flow or oral microflora (such as antibiotics);Children with mental or cognitive problems; andPatients with maxillary anterior permanent teeth affected by disturbances in the development of dental structures (hypoplasia, hypomineralization, fluorosis).

#### Interventions

A low-speed rubber cup and pumice paste (CleanPolish, Kerr) will be used for 30 s for cleaning and polishing of the maxillary anterior teeth and then they will be washed for debris and organic residue removal. A baseline visual inspection using ICDAS criteria of the vestibular surfaces of the investigated teeth as well as white and blue light digital photographs using the device SoproLife® (Sopro-Acteon group, La Ciotat, France) will be made.

##### Topical fluoride application protocol

(according to the instructions for use of the manufacturer):
Following the instructions of the dosing guide, the required amount of the varnish (Clinpro™ White Varnish 5% Sodium Fluoride, 3 M ESPE, USA) is determined—0.5 mlIsolationOpening of the unit-dose package of the varnish and dispensation of the entire content onto the round dosing guide on the back of the foil pouch followsSince components of all sodium fluoride varnishes can separate during storage, thoroughly mixing with the applicator brush is requiredApplication of the varnish evenly in a thin layer over the whole vestibular surfaces of all anterior maxillary teeth with sweeping, horizontal brush strokes. No suction is required

##### Laser irradiation protocol

The vestibular surfaces of the left maxillary anterior teeth will be exposed to CO_2_-laser (Ultra Dream Pulse, DS_40U, Daeshin Enterprise, Seoul, South Korea), emission wavelength 10,600 nm. The parameter settings used will be:

Time on—100 μs, time off—40 ms;

Average power—0.73 W; peak power—292.73 W;

Speed of movement—2 mm/s;

Energy density with movements—5 J/cm^2^;

Tip-to-tissue distance—20 mm; tip diameter 700 μm; and

Irradiation time—30 s.

The measured values were confirmed using a power meter. The chosen protocol parameters are modified in a previously conducted study [5].

##### Placebo protocol

The vestibular surfaces of the right maxillary anterior teeth are exposed to sham light (as a placebo light). No pulse energy will be applied.

##### Bonding brackets protocol

*Bonding brackets protocol* includes the following steps:
IsolationTooth surfaces will be etched with 35% phosphoric acid gel (Etching gel, DMP Ltd.) for 30 s and rinsed for the same timeReisolationTooth surfaces will be dried with air spray for 15 sAn adhesive bonding agent (AdperTM single bond, 3 M ESPE, USA) will be applied on the enamel surfaces according to the manufacturer’s instruction, and then will be cured for 20 sFluoride-free Transbond XT resin composite (3 M Unitek, USA) will be applied, and a stainless steel orthodontic bracket with a slot size of 22 (3 M Unitek, USA) will be placed while excess composite will be removed. Resin composites will be cured for 20 s of occlusal, gingival, mesial, and distal directions.

The patient will be recalled 6 and 12 months post-irradiation. A visual inspection and reapplication of the fluoride varnish will be conducted by the same operator. During the evaluation, the teeth will be thoroughly cleaned with a rubber cup and pumice and then washed. After drying, the vestibular surfaces will be visually evaluated using ICDAS and SoproLife® daylight and blue fluorescence, followed by topical fluoride application.

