#### Clinical protocol

First visit:
Parents/guardians are informed about the protocol of the study and the laser technique. They sign the informed consent form (see Supplementary data file S2 “Patient consent form”). Verbal assent from the child is obtained.The teeth are cleaned and polished with a rubber cup and pumice paste.A visual inspection of the vestibular surfaces of the investigated teeth and SoproLife® Daylight and SoproLife® Blue fluorescence digital images are made and recorded.Application of fluoride varnish Clinpro™ White Varnish 5% Sodium Fluoride over the whole vestibular surfaces of all anterior maxillary teethThe chosen method, CO_2_-laser irradiation or placebo, is applied.Follows direct adhesive bonding of orthodontic brackets

Second visit:
The teeth are cleaned and polished with a rubber cup and pumice paste.The incidence, extent, and severity of the lesions are assessed using ICDAS criteria and SoproLife® daylight and blue fluorescence. The data are recorded and digital photographs are made.Reapplication of the fluoride varnish Clinpro™ White Varnish 5% Sodium Fluoride

Third visit:
The teeth are cleaned and polished with a rubber cup and pumice paste.The incidence, extent, and severity of the lesions are assessed using ICDAS criteria and SoproLife® daylight and blue fluorescence. The data are recorded and digital photographs are made.Reapplication of the fluoride varnish Clinpro™ White Varnish 5% Sodium Fluoride

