### Outcomes

#### Primary outcome measures

The primary outcome measures are the number of newly appeared caries lesions and the changes into ICDAS scores in the experimental and control teeth (within one patient) from baseline to 12 months. The International Caries and Detection System (ICDAS) is a visual scoring system developed for use in clinical assessment and clinical research of caries development and progression. It uses a numbered scoring system with a range from 0 to 6, to grade enamel demineralization and cavitation. Code of “0” represents unaffected/sound enamel, no caries change; “1” first visual change represents initial demineralization that is visible only after air drying; “2” represents a distinct visual change in the enamel that is visible when the surface is wet; “3” represents localized enamel loss or breakdown, no visible dentin or underlying shadow; and “4-6” represent larger carious lesions in dentin. Time frame: 1 year.

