#### Blinding

As participants in the treatment as well as the nature of the intervention, the operator and the dental assistant will not be blinded to subjects’ group assignments. The patient will be also not blind to the treatment. The dental assistant will inform the doctor which protocol will be the first to start with and which will be the second protocol. The statistician will be blinded to treatment assignment as data will be masked before the analysis by labeling the 2 quadrants as 0 and 1, without giving the statistician the key.

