## Statistical methods

The obtained data will be recorded, tabulated, processed, and analyzed using SPSS (Statistical Package for Social Science software) version 21.0 (IBM, USA). Descriptive statistics will be calculated. For the split-mouth randomized controlled trial Student t-test for paired samples will be used for the analysis. Mixed effects proportional odds regression modeling with outcomes of ICDAS and SOPROLIFE scores will be calculated. The inter-observer reliability and agreement will be estimated by Kappa coefficient where Kappa coefficient values above 0.80 are considered acceptable. Missing Completely at Random (MCAR) will be used to handle the missing data.

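### The visual ICDAS outcome is scored at 6 and 12 months by an unmasked operator who knows the laser side, and the photographs already planned are not used for a masked reading

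*Protocol article*

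**What the plan says.** - **Outcome.** The section on the primary outcome reads: "The primary outcome measures are the number of newly appeared caries lesions and the changes into ICDAS scores in the experimental and control teeth", from baseline to 12 months. The same section says that ICDAS "is a visual scoring system developed for use in clinical assessment and clinical research of caries development and progression". Code 1 is a change seen only after air drying; code 2 is visible on a wet surface.
- **Who scores.** The recall paragraph under Bonding brackets protocol: "A visual inspection and reapplication of the fluoride varnish will be conducted by the same operator". It goes on to ICDAS and SoproLife evaluation at that visit.
- **Who is masked.** The text after Table 1 (Trial design): "the doctor, dental assistant, and the patient are not blinded and the trial is an unmasked, open-label trial". Blinding: "the operator and the dental assistant will not be blinded". The only masked role is in the same section: "The statistician will be blinded to treatment assignment as data will be masked before the analysis".
- **Side.** Trial design, Laser irradiation protocol and Participant's timeline all put the laser on the left maxillary anterior teeth. Sequence generation speaks of allocating quadrants but then describes randomising only the order of the two procedures.
- **Photographs.** White- and blue-light SoproLife images are taken at baseline (Interventions; Clinical protocol, first visit). At each recall visit, Clinical protocol says: "The data are recorded and digital photographs are made".
- **Second observer.** Statistical methods: "The inter-observer reliability and agreement will be estimated by Kappa coefficient". No section says who the observers are, what they score, whether they are masked, or whose score is analysed.

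**The concern.** The protocol justifies the lack of masking by the nature of the interventions. That reason covers the person holding the laser at the first visit. It does not cover grading enamel 6 and 12 months later, which is a separate task.

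In a split-mouth trial the examiner sees both sides of the same mouth together and, under this protocol, knows that left means laser. Any expectation then acts directly on the within-patient contrast that the trial estimates. All study teeth start at ICDAS 0 (Inclusion criteria), so a tooth counts as worsened on its first upward call, and that call is a visual judgement. Labelling the quadrants 0 and 1 for the statistician cannot remove a bias already in the recorded scores. An inter-observer kappa would not reveal it either if both observers were unmasked and shared the same expectation.

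**Working it through.** **Inputs** (Sample size calculation): control incidence p1 = 8.7%; laser incidence p2 = 3.6%; 41 patients; three anterior teeth per side, so 41 × 3 = 123 teeth per side.

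**Plan's own figure.** The formula, with both exponents read as squares, two-sided 5% and 80% power, gives (1.960 + 0.842)² × (0.087 × 0.913 + 0.036 × 0.964) / 0.051² = 344.4, so 345 teeth per group. The stated 121 per group is not reproduced. That is a separate matter; the present point does not depend on it.

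**Step 1: size of the planned effect in teeth.**
- Control: 123 × 0.087 = 10.7 lesions.
- Laser: 123 × 0.036 = 4.4 lesions.
- Difference: 123 × 0.051 = 6.3 teeth.

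**Step 2: what a gap of that size would show.** With teeth treated as independent, pooled p = 0.0615 and SE = √(0.0615 × 0.9385 × 2/123) = 0.0306. Then z = 0.051/0.0306 = 1.66 and two-sided p is about 0.10. Whole counts of 11 versus 4 give Fisher p = 0.11. A gap equal to the planned difference would therefore not in itself be significant at this sample size.

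**Step 3: how much misscoring would make that gap.** If the true rate were 8.7% on both sides, under-calling alone would have to miss 6.3 of 10.7 laser-side lesions, or 59%. Smaller shifts still move the estimate.

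**Step 4: sensitivity of the false-positive rate.** Assume no true effect and 8.7% on both sides. A fraction m of laser-side lesions is missed, and a fraction u of sound control teeth is called a lesion. The observed rates are a = 0.087 + 0.913u (control) and b = 0.087(1 − m) (laser). The table gives the chance of two-sided p < 0.05 in a two-proportion test with 123 teeth per side:

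| m | u = 0 | u = 1% | u = 2% |
|---|---|---|---|
| 10% | 5.7% | 7.8% | 11.3% |
| 20% | 8.0% | 11.7% | 16.7% |
| 30% | 12.2% | 17.6% | 24.2% |

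For example, m = 20% and u = 1% give a = 9.6% and b = 7.0%, an apparent benefit of 2.7 percentage points (about 3.3 teeth) where none exists. The values of m and u are assumptions, teeth are treated as independent, and the test is a simple stand-in for the paired and mixed-model analyses that are planned.

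**The case against.** The open-label status is declared openly, and several stronger readings go beyond the text.

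- **A second observer is already available at recall.** A reader might infer this from the kappa. The protocol names no such person, and the kappa could come from a calibration exercise. A second examiner at every recall may be new staff. This objection stands.
- **The lesions at stake are mostly borderline calls between codes 0 and 1.** The protocol gives incidences only, with no breakdown by code. Some lesions may be code 2 and less open to judgement. This stands.
- **Misscoring six teeth would make or break the trial.** Six teeth equal the planned difference, but Step 2 gives p of about 0.10 for that gap, and Step 3 shows that under-calling alone would need a 59% miss rate to produce it. The documents support a material shift in the estimate, not a reversed conclusion.
- **Masking a chairside examiner is simple.** It is not while the laser is always on the left. It needs side to be randomised, so it waits on reconciling Sequence generation with the sections that fix the side.
- **Photographs can replace ICDAS.** They cannot do so fully, because codes 1 and 2 differ by dry versus wet viewing.
- **The same operator** could mean one examiner for both recalls rather than the person who gave the treatment. The treating operator is the more natural reading, and under either one no masked assessor is described.

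None of this supplies a reason for unmasked scoring of a visual primary outcome.

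**Conclusion.** The concern holds in a limited form. The protocol assigns a visual primary outcome to an unmasked operator who knows the treated side, and its stated reason for not masking does not extend to the recall scoring. Masking the statistician does not close the gap.

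The planned effect is about 6 teeth (10.7 versus 4.4 lesions, 123 per side), so side-dependent scoring of a few teeth could materially change the estimate. Under the assumed error rates above, the false-positive rate rises from 5% to between 5.7% and 24.2%. Those rates are illustrative. The documents do not show that bias will occur, how large it would be, or that the examiner expects benefit. Bias towards the laser is the direction to guard against, not an established fact.

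Confidence is high for the missing masked assessment and low for any particular size of bias. A masked reading of images that are being taken anyway is an inexpensive improvement, whereas bias in the recorded scores cannot be removed by analysis afterwards.

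**What to change.** 1. State that the baseline, 6- and 12-month SoproLife photographs will be coded, cropped by quadrant, mirror-flipped so that left and right look alike, and put in random order. Flipping conceals the side even if the laser stays on the left.
2. Have them scored for lesion or no lesion (ICDAS codes 1 and 2 pooled) and for SoproLife grade by an observer already in the study. Preferably this is the kappa observer, provided that person did not deliver treatment. Otherwise it is the operator, after the last 12-month visit. The second option is weaker, because the operator has already seen these mouths.
3. Make this reading the main SoproLife analysis and a prespecified masked analysis of lesion incidence beside the chairside ICDAS score. Report agreement between the two.
4. State who the kappa observers are, what they score, and whether they are masked.
5. Reconcile Sequence generation with Trial design, Laser irradiation protocol and Participant's timeline on how the side is assigned. If side is then truly randomised and the kappa observer already attends recalls, use that observer's masked chairside ICDAS score as primary.

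**Cost.** Protocol wording and some hours of image coding and reading. Items 1 to 3 need no new visit or image. The downside is that images may not separate ICDAS 1 from 2, so the image analysis addresses lesion incidence and not the full ordinal score. Item 5 could need extra staff if no second observer attends recalls, which is why it is conditional.
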